#### Primary outcomes

Consistent with the pilot nature of the trial, primary outcomes focus on feasibility, acceptability and implementation fidelity rather than definitive clinical effectiveness.

Feasibility outcomes include recruitment rate, defined as the proportion of eligible individuals who consent and are randomised; retention rate, defined as the proportion of randomised participants completing the 12-month follow-up; and intervention adherence, defined as the proportion of participants in the CCT arm attending at least nine of the 12 sessions.Acceptability is assessed using the CSQ-8, administered at the 3-month assessment. The CSQ-8^31^ is a widely used measure of service satisfaction, with higher scores indicating greater perceived acceptability.Implementation fidelity is evaluated through independent coding of a random 20% sample of audio-recorded CCT sessions. Fidelity ratings assess both adherence to manualised content and quality of delivery, providing an objective index of whether task-shifted delivery maintains intervention integrity.

#### Secondary outcomes

Secondary outcomes are included to generate preliminary estimates of effect size and variability, informing the design of a future definitive trial.

Global cognitive functioning is measured using the composite z-score of the BACS,^33^ a validated battery assessing processing speed, verbal memory, working memory, executive function and attention.Functional capacity is assessed using an adapted version of the UPSA-N^34^, which evaluates participants’ ability to perform everyday tasks such as financial management, communication and planning.Psychiatric symptom severity is measured using the Brief Psychiatric Rating Scale-18 (BPRS-18),^39^ a clinician-rated instrument assessing positive, negative and affective symptoms.Real-world disability is assessed using the 12-item version of the WHO Disability Assessment Schedule 2.0,^40^ capturing functional limitations across multiple life domains.Quality of life is assessed using the Manchester Short Assessment of Quality of Life,^41^ supplemented by global items from the WHO Quality of Life-BREF^42^ to enhance cross-study comparability.Social cognition, a domain increasingly recognised as central to functional recovery, is assessed using the adapted and contextualised version of the Social Cognition Screening Questionnaire^43^ at baseline and at the 12-month follow-up only, reflecting its relative stability over shorter intervals.

#### Economic outcomes

Resource use and costs are assessed using an adapted Client Service Receipt Inventory (CSRI),^44^ capturing utilisation of formal healthcare services, informal care, non-orthodox care (including traditional and faith-based services) and productivity losses. Health-related quality of life is measured using the EQ-5D-5L^45^ to support exploratory cost–utility analyses.

A comprehensive summary of outcome domains, the specific instruments employed and their respective assessment schedules is provided in table 2.

**Table 2 T2:** Outcome domains, instruments and assessment time points

Outcome domain	Measure	Outcome type	Assessment time points
Feasibility	Recruitment rate	Primary	Screening to randomisation
	Retention rate	Primary	3, 6 and 12 months
	Session attendance	Primary	During intervention
Acceptability	Client Satisfaction Questionnaire-8	Primary	3 months
Implementation fidelity	CCT fidelity checklist (audio-coded)	Primary	During intervention
Global cognition	Brief Assessment of Cognition in Schizophrenia composite	Secondary	Baseline, 3, 6, 12 months
Functional capacity	UCSD Performance-Based Skills Assessment–Nigeria	Secondary	Baseline, 3, 6, 12 months
Psychiatric symptoms	Brief Psychiatric Rating Scale-18	Secondary	Baseline, 3, 6, 12 months
Disability	WHO Disability Assessment Schedule 2.0 (12-item)	Secondary	Baseline, 3, 6, 12 months
Quality of life	Manchester Short Assessment of Quality of Life	Secondary	Baseline, 3, 6, 12 months
	WHO Quality of Life-BREF (global items)	Secondary	Baseline, 3, 6, 12 months
Social cognition	Social Cognition Screening Questionnaire–Nigeria	Exploratory	Baseline, 12 months
Health-related quality of life	EQ-5D-5L	Economic	Baseline, 12 months
Resource use and costs	Client Service Receipt Inventory	Economic	Baseline, 12 months

CCT, compensatory cognitive training.

### Data collection management

#### Data collection procedures

All assessments are conducted face-to-face in private consulting rooms within participating hospitals or, where necessary, at alternative agreed locations to support retention. Data are entered directly into electronic case report forms using password-protected tablets. The electronic system is hosted on REDCap, configured with built-in logic checks, range validations and audit trails to enhance data quality.

Paper-based forms are available as backup and are transcribed into the electronic database within 48 hours. Research assistants undergo rigorous training lasting 3–5 days, covering standardised assessment administration, maintenance of blinding and procedures for managing participant distress or clinical risk.

Prior to trial commencement, inter-rater reliability for clinician-rated instruments (eg, BPRS-18, UPSA-N) will be established using joint rating exercises based on standardised case vignettes and recorded interviews. ICC will be calculated, with a threshold of ≥0.80 required before independent assessment is permitted. During the study, periodic reliability recalibration sessions will be conducted every 6 months, and 10% of assessments will be independently double-rated to monitor drift. Where ICC falls below 0.75, retraining will be implemented.

#### Data security and confidentiality

All electronic data are encrypted during transmission and at rest on secure servers hosted by Lagos State University College of Medicine. Access to the REDCap database is role-based and restricted to authorised research personnel using unique login credentials. Personal identifiers are stored separately in an encrypted key file linked to study data only via unique participant identification numbers. In accordance with funder and regulatory requirements, anonymised data will be retained for a minimum of ten years following study completion.

### Quantitative data analysis

#### General analytic principles

All quantitative analyses will be conducted in accordance with a pre-specified Statistical Analysis Plan finalised prior to database lock. Analyses will be performed using Stata V.18 or R V.4.3.0. The primary analysis population is defined according to the intention-to-treat principle, with all randomised participants analysed in their assigned groups regardless of intervention adherence or withdrawal. A per-protocol analysis, restricted to participants attending at least 75% of intervention sessions, will be conducted as a sensitivity analysis.

#### Analysis of primary outcomes

Given the pilot design, analyses of feasibility and acceptability outcomes are descriptive in nature, focusing on estimation rather than hypothesis testing. Recruitment, retention, adherence and satisfaction outcomes will be summarised using proportions or means with corresponding 95% CIs. The lower bounds of these CIs will be evaluated against prespecified ‘traffic light’ criteria to inform progression decisions.

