#### Primary objectives: feasibility and acceptability

**Objective 1 (Feasibility):** To assess the feasibility of recruiting and retaining young adults with FEP into a longitudinal cognitive intervention trial across three public psychiatric hospitals. It is anticipated that recruitment of 180 participants within a 9-month enrolment period will be achievable, corresponding to the recruitment of at least 60% of eligible individuals screened. Retention of at least 70% of randomised participants at the 12-month follow-up is expected. Among participants allocated to CCT,^19^ it is anticipated that at least 75% will attend a minimum therapeutic dose, defined as nine or more of the twelve sessions.**Objective 2 (Acceptability):** To evaluate the acceptability of the culturally adapted CCT intervention among service users and facilitating staff. Acceptability will be operationalised through participant satisfaction scores, with the expectation that mean scores on the Client Satisfaction Questionnaire-8 (CSQ-8)^31^ will reach or exceed 24 out of a possible 32 at the 3-month assessment.**Objective 3 (Fidelity):** To determine whether CCT can be delivered with adequate fidelity and competence by non-specialist health workers within a task-shifted model. It is anticipated that trained psychiatric social workers will achieve at least 80% adherence to manualised content and delivery competence benchmarks, based on independent coding of a sample of audio-recorded sessions.

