### Sample size and pilot rationale

The target sample size is 180 participants, with 90 allocated to each trial arm. In keeping with established guidance for pilot and feasibility trials, the sample size has been selected to provide adequate precision around key feasibility parameters rather than to ensure statistical power for hypothesis testing of clinical outcomes.

Assuming a conservative retention rate of 70%–75% at the 12-month follow-up, a sample of 180 participants allows estimation of retention with a 95% CI width of approximately ±7%. This level of precision is sufficient to apply prespecified ‘traffic light’ progression criteria to inform decisions regarding advancement to a definitive trial.

Although the study is not powered for definitive efficacy analyses, the planned sample size is expected to be sufficient to detect preliminary clinical signals. With 90 participants per arm, allowing for attrition, the study retains approximately 80% power at a two-sided alpha level of 0.05 to detect a medium effect size (Cohen’s d=0.50) on the BACS composite score. This calculation accounts for clustering effects associated with group-based intervention delivery, assuming an intraclass correlation coefficient (ICC) of 0.05.

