### Progression criteria for a definitive trial

As a pilot feasibility study, progression to a future definitive randomised controlled trial will be guided by prespecified criteria using a structured ‘traffic light’ framework. This framework integrates quantitative feasibility metrics with qualitative insights from the embedded process evaluation, allowing progression decisions to be informed not only by whether targets are met, but also by why they are met or missed.

**Green (Go):** Progression to a definitive trial will be recommended if recruitment rates meet or exceed 60%, retention at the 12-month follow-up meets or exceeds 70%, and intervention fidelity reaches at least 80% adherence to manualised content. Under this scenario, only minor protocol refinements would be required.**Amber (Amend):** If feasibility targets are narrowly missed but remain within a remediable range (eg, recruitment of 40%–59% or retention of 50%–69%), progression may still be recommended, conditional on targeted protocol modifications. Such modifications may include adjustments to recruitment pathways, increased participant reimbursement or refinements to intervention delivery identified through process evaluation findings.**Red (Stop):** Substantial shortfalls in feasibility (eg, recruitment below 40% or retention below 50%) will prompt a recommendation not to proceed to a definitive trial without fundamental redesign.

Progression to a future definitive trial will be guided by pre-specified 'traffic light’ criteria, integrating quantitative metrics with qualitative insights (table 3). Importantly, quantitative thresholds will not be interpreted in isolation. The Trial Steering Committee will explicitly prioritise triangulation with qualitative data to understand contextual drivers of feasibility outcomes. For example, if retention falls within the ‘Amber’ range but qualitative interviews indicate transport costs as the primary barrier, progression may still be endorsed contingent on addressing this barrier in future trial design.

**Table 3 T3:** Progression criteria for definitive randomised controlled trial (‘traffic light’ framework)

Domain	Green (Go)	Amber (Amend)	Red (Stop)
Recruitment rate	≥60% of eligible participants randomised	40%–59% randomised	<40% randomised
Retention at 12 months	≥70% retained	50%–69% retained	<50% retained
Intervention adherence	≥75% attend ≥9 sessions	60%–74% attend ≥9 sessions	<60% attend ≥9 sessions

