Acceptability (CSQ-8)	Mean score ≥24	Mean score 20–23	Mean score <20
Intervention fidelity	≥80% adherence and competence	65%–79% adherence	<65% adherence
Qualitative feasibility	No major unresolvable barriers identified	Barriers identified but remediable	Fundamental barriers to delivery

Progression decisions will be based on triangulation of quantitative metrics with qualitative process evaluation findings rather than on any single criterion alone.

CSQ-8, Client Satisfaction Questionnaire-8.

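### The protocol compares confidence limits with the traffic-light cut-offs in one section and reads as applying the same cut-offs to the rates and means in another, without saying which sets the colour

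*Protocol article*

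**What the plan says.** Under Analysis of primary outcomes, recruitment, retention, adherence and satisfaction are to be "summarised using proportions or means with corresponding 95% CIs". The next sentence adds: "The lower bounds of these CIs will be evaluated against prespecified" traffic-light criteria, to inform progression.

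Under Progression criteria for a definitive trial, Green requires among other things that "retention at the 12-month follow-up meets or exceeds 70" per cent. Table 3 gives the Green cells as "≥60% of eligible participants randomised", "≥75% attend ≥9 sessions" and "Mean score ≥24" for recruitment, adherence and CSQ-8. Neither the text nor the table mentions a confidence limit. Amber for retention is 50%–69% and Red is below 50%. For adherence, Amber is 60%–74% and Red is below 60%.

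The planning values are close to the cut-offs. The primary objectives state "Retention of at least 70% of randomised participants at the 12-month follow-up is expected", with corresponding floors of 60% for recruitment, 75% for adherence and a mean of 24 for CSQ-8. The sample size section begins "Assuming a conservative retention rate of 70%–75% at the 12-month follow-up". It derives a precision of about ±7% and calls that sufficient to apply the criteria.

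The progression section and the note to Table 3 also say that the thresholds are read together with the qualitative findings and that no single criterion decides.

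**The concern.** The two sections appear to name different decision statistics for the same cut-offs. A lower limit always sits below its estimate, so the two rules can colour the same data differently. The gap bites here because the Green cut-offs are set at, or just below, the values the protocol plans on.

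Feasibility and acceptability are the primary outcomes, and the progression recommendation is a main product of the pilot. If the statistic is not fixed beforehand, the colour of a result near a boundary can be settled after the data are seen, which defeats the purpose of prespecified criteria.

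**Working it through.** **Inputs from the protocol.** n = 180 in total and 90 in the CCT arm. Green cut-offs are 70% retention, 75% adherence, 60% recruitment and a CSQ-8 mean of 24. Planning values are 70%–75% retention, at least 75% adherence and at least 60% recruitment.

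**Assumptions.** The 95% intervals are two-sided. There are 180/0.60 = 300 eligible people. Counts are binomial, with no adjustment for therapy-group clustering. The protocol article does not name the interval method, so Wald, Wilson and Clopper–Pearson were all tried.

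**1. The stated precision.** Half-width = 1.96 × √(p(1−p)/180).
- p = 0.70: 1.96 × √(0.21/180) = 0.067.
- p = 0.75: 1.96 × √(0.1875/180) = 0.063.

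The ±7% reproduces.

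**2. Results exactly on plan.** The Wald lower limit is p − 1.96 × √(p(1−p)/n). For 126/180 it is 0.700 − 0.067 = 0.633.

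| Result | Observed | Lower limit, Wald | Lower limit, Wilson | Colour on rate | Colour on lower limit |
|---|---|---|---|---|---|
| Retention 126/180 | 70.0% | 63.3% | 62.9% | Green | Amber |
| Retention 135/180 | 75.0% | 68.7% | 68.2% | Green | Amber |
| Adherence 68/90 | 75.6% | 66.7% | 65.8% | Green | Amber |
| Recruitment 180/300 | 60.0% | 54.5% | 54.4% | Green | Amber |

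For CSQ-8 the article gives no SD. With assumed SDs of 3 to 6 and n of 63 to 90, an observed mean of 24 has a lower limit (24 − 1.96 × SD/√n) between 22.5 and 23.4, short of the Green value.

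**3. Smallest count whose lower limit reaches the Green cut-off.**
- Retention: 138/180 (76.7%) by Wald, 139/180 (77.2%) by Wilson or Clopper–Pearson.
- Adherence: 75/90 (83.3%) by Wald, 76/90 (84.4%) by the other two.
- Recruitment: 197/300 (65.7%) by Wald or Wilson, 198/300 (66.0%) by Clopper–Pearson.

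**4. Chance of Green on each measure**, as the exact binomial probability of reaching the required count. The ranges span the interval methods.

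| Measure | True rate | Lower-bound rule | Observed-rate rule |
|---|---|---|---|
| Retention | 70% | 1.9%–2.9% | 53.7% (≥126/180) |
| Retention | 75% | 27.7%–33.8% | 94.7% |
| Retention | 80% | 84.7%–88.6% | over 99.9% |
| Adherence | 75% | 2.2%–4.0% | 50.8% (≥68/90) |
| Recruitment | 60% | 1.9%–2.5% | 52.5% (≥180/300) |

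Under the lower-bound rule, true retention must be about 79%–79.5% for an 80% chance of Green on retention.

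**5. The Stop boundary.** For 103/180 (57.2%) the lower limit is 49.99% by Wald and 49.9% by Wilson. For 104/180 it is 50.6% and 50.5%. Observed retention from 90/180 to 103/180 (50.0%–57.2%) is therefore Amber on the rate and Red on the lower limit. At 107/180 (59.4%), the middle of the Amber band, the lower limit is about 52% and the result stays Amber.

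**The case against.** The strongest reply is that there is no contradiction. Table 3 supplies cut-offs and never uses the word observed, while the analysis section supplies the quantity compared with them. On that reading the lower bound simply governs. This is possible, but the progression section states its rule in full as a rate meeting a threshold, and its plain reading is the rate itself. A reader of that section alone would not apply a confidence limit, and no text connects the two.

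Second, the planning values are mostly floors, and the retention range is called conservative. Requiring the lower limit to clear a floor is a legitimate, stricter rule, and at true retention of 80% it gives Green 85%–89% of the time. This stands. A reader might infer that a trial running to plan can almost never be Green. The protocol does not support that in general: about 2%–4% applies to a measure whose true rate sits exactly on its cut-off, while 75% retention, inside the planning range, gives 28%–34%.

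Third, the colours are not mechanical. The analysis section says the bounds inform decisions, Amber may still lead to progression, and the steering committee weighs qualitative findings. This also stands, so it would be too strong to say that the Go, Amend or Stop decision itself turns on which section is followed. But this text governs how colours are weighed, not which statistic produces them.

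Finally, one might infer that mid-Amber results become Red. Only the lower part of the retention band does.

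**Conclusion.** The point holds as an unresolved choice of decision statistic. Results exactly on plan for recruitment, retention and adherence are Green on the rate and Amber on the lower limit. An observed CSQ-8 mean of 24 behaves the same way in falling short of Green, whatever the SD. The lower-bound rule raises the practical Green requirement to about 77% retention, 83%–84% adherence and 66% recruitment, and moves observed retention of 50.0%–57.2% from Amber to Red.

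The ±7% figure is arithmetically right. It is reasonable for telling 70% from the 50% Stop boundary. It does not support Green at the planned retention if the lower limit decides, since even an observed 75% has a lower limit below 70%.

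The recruitment figures rest on the assumed 300 eligible people and the CSQ-8 figures on assumed SDs. Clustering by therapy group is ignored, and allowing for it would widen the adherence interval. Fidelity is not among the outcomes for which the analysis section specifies intervals, so it is outside this point.

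**What to change.** Name one decision statistic, in the same words, under Analysis of primary outcomes and in the progression section with Table 3, for recruitment, retention, adherence and CSQ-8. There are two coherent options.

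1. **Point estimate.** Assign the Table 3 zones by the observed rate or mean, report the 95% CI beside it, and change the sentence that compares lower bounds with the criteria. A further condition that the lower limit clear the Red boundary would add nothing: at these sizes any result meeting the Green rate already does so (Wilson limits 62.9% against 50% for retention, 65.8% against 60% for adherence, 54.4% against 40% for recruitment).
2. **Lower bound.** Keep the stricter rule, say so in the progression section and Table 3, reset the cut-offs below the planning values, and revise the claim that ±7% precision is sufficient. As a guide to distance, the present 70% retention cut-off needs a true rate about 9 points higher for an 80% chance of Green.

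Option 1 costs about two sentences. Option 2 also means revisiting Table 3 and the sample size text. Neither needs more participants or data, and either should be settled before outcome data are seen.

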#### Analysis of secondary outcomes

Preliminary clinical signals will be explored using linear mixed-effects models to account for repeated measures over time and to accommodate missing data under a missing-at-random assumption. Models will include fixed effects for treatment group, time and their interaction, with random intercepts specified for participants and therapy groups to account for within-subject correlation and clustering.

Models will be adjusted for baseline outcome values, study site and age stratum. The primary parameter of interest is the adjusted mean difference between groups at the 12-month endpoint. Standardised effect sizes (Cohen’s d) with 95% CIs will be calculated to inform future power calculations. P values will be reported but interpreted cautiously, recognising the exploratory nature of the analyses.

#### Missing data

Patterns and predictors of missingness will be examined to assess the plausibility of the missing-at-random assumption. Where missing data exceed 15% for key outcomes, sensitivity analyses using multiple imputation by chained equations will be conducted, generating 20 imputed datasets.

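### The stated missing-data sensitivity analysis rests on the same missing-at-random assumption as the main model, so it cannot show how the 12-month difference would move if that assumption fails

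*Protocol article*

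**What the plan says.** Under Analysis of secondary outcomes, the Protocol article fits linear mixed-effects models "to accommodate missing data under a missing-at-random assumption". The parameter of interest is the adjusted between-group difference at 12 months. Cohen's d with its 95% CI is to be calculated for use in later power calculations.

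The Missing data section first proposes to look at patterns and predictors of missingness to judge whether MAR is plausible. It then states: "Where missing data exceed 15% for key outcomes, sensitivity analyses using multiple imputation by chained equations will be conducted, generating 20 imputed datasets". It mentions no offset, reference-based, pattern-mixture or tipping-point element. The only other sensitivity analysis, under General analytic principles, is a per-protocol analysis, which concerns attendance and not missing outcomes.

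On expected loss, Sample size and pilot rationale says: "Assuming a conservative retention rate of 70%–75% at the 12-month follow-up". The primary objectives say: "Retention of at least 70% of randomised participants at the 12-month follow-up is expected".

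**The concern.** A sensitivity analysis for missing data should vary the assumption that the main analysis cannot verify. Here that assumption is MAR: given what was observed, participants without a 12-month score resemble those with one. The mixed model relies on it, and so does standard chained-equations imputation. The second analysis may condition on more variables, but it does not depart from MAR.

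The descriptive check does not fill the gap. Observed data can show that missingness is related to measured variables. They cannot show whether it also depends on the unseen 12-month score, and this is what separates MAR from missing not at random (MNAR).

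What is at stake is the d handed to the designers of the definitive trial. If people who deteriorate are less likely to return, and more so in one arm, the main model and the imputation can be wrong together and agree closely. The CI would give no warning, since it reflects sampling error under MAR only.

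**Working it through.** **Inputs from the Protocol article.** 180 participants, 90 per arm; 12-month retention 70–75%; 15% trigger; reference effect d = 0.50 (all from Sample size and pilot rationale, except the trigger, which is in Missing data). The offsets (delta, in SD units) are assumptions; the documents give none.

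**1. The plan's own figure.** The half-width of the 95% CI for retention is 1.96 × √(p(1−p)/180).
- p = 0.70: 1.96 × √(0.21/180) = 0.067
- p = 0.75: 1.96 × √(0.1875/180) = 0.063

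The stated precision of about ±7 percentage points reproduces.

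**2. Is the trigger likely to be met?** Loss is 25–30%, or 0.25 × 180 = 45 to 0.30 × 180 = 54 participants. Read at the 12-month visit, the trigger would be avoided only with retention of 85% or more (100 − 15). A trial that just reaches its Green retention threshold of 70% has twice the trigger level missing.

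**3. Size of a departure from MAR.** Let f be the missing fraction in an arm and delta the amount by which its missing outcomes are worse than MAR predicts. Then:

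fall in the difference = f(CCT) × delta(CCT) − f(control) × delta(control)

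Offset in the CCT arm only:

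| Missing | Delta | Fall | What remains of d = 0.50 |
|---|---|---|---|
| 25% | 0.3 | 0.075 | 0.425 |
| 30% | 0.3 | 0.09 | 0.41 |
| 25% | 0.5 | 0.125 | 0.375 |
| 30% | 0.5 | 0.15 | 0.35 |

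Equal loss and equal offset in both arms: 0.30 × 0.5 − 0.30 × 0.5 = 0. Unequal loss with equal offset, for example 30% against 25% at delta 0.5: 0.15 − 0.125 = 0.025. An offset in the control arm only would raise the difference by the amounts in the table.

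Taking d = 0.50 to zero needs a CCT-only offset of 0.50/0.25 = 2.0 SD or 0.50/0.30 = 1.67 SD.

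**4. What it means for a later sample size.** Required numbers scale with 1/d². If 0.50 is reported and the true value is 0.425, the ratio is (0.50/0.425)² = 1.38. At 0.35 it is (0.50/0.35)² = 2.04.

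**5. Can the two planned analyses agree while both are wrong?** An illustrative simulation used 200 runs, n = 180, true d = 0.50, an assumed correlation of 0.6 between visits, and 30% missing overall at 12 months only. It compared a mixed model with 20-fold regression-based imputation using arm and the outcome's own earlier values, without auxiliaries or therapy-group effects.
- Under MAR: mixed model 0.501, imputation 0.501; mean absolute gap 0.017.
- With missingness in the CCT arm depending on the unseen 12-month score: mixed model 0.688, imputation 0.695; mean absolute gap 0.020.

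Both methods were off by about 0.19 SD in the second setting, yet they agreed almost as closely as in the first. The size of that bias follows from the chosen mechanism and is not a prediction for this trial.

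**The case against.** The strongest reply is that a separate statistical analysis plan is announced and not shown, and that MNAR analyses, the choice of offsets and the imputation model are normally settled there. This stands in part. A reader might infer that the trial has no MNAR analysis at all; the article cannot support that. But the article is not silent: it names the method, the trigger and the number of imputations, and calls the result a sensitivity analysis. The point is about that stated choice.

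A second reply is that imputation is not empty repetition. It can bring in earlier BPRS-18 scores, disability, quality of life and attendance, which the mixed model does not use. If relapse shows up there first, a shift in the estimate would be informative. This stands: it would be too strong to say that nothing is tested. The simulation used no auxiliaries, so close agreement was to be expected. The imputation still cannot explore dependence on the unseen score itself.

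Third, the size is an illustration. Nothing in the documents says that CCT dropouts do worse than control dropouts, and the arms are matched on sessions, duration, group size and reimbursement. A reader might infer that d will be overstated by a quarter or more; that would need a one-arm offset that the documents neither state nor imply. The shift is also smaller than the sampling error: with 63 to 67.5 completers per arm, 1.96 × √(2/n) is about 0.35 to 0.34, before clustering or baseline adjustment.

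Fourth, 70–75% is described as conservative, so meeting the trigger is likely and not certain.

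Finally, the outcome is exploratory, the article urges caution in interpreting it, and no efficacy estimate enters the progression criteria. This limits the priority.

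**Conclusion.** The point holds in a limited form. The stated sensitivity analysis and the main model share the MAR assumption, and neither the imputation nor the descriptive look at missingness can show how the 12-month difference depends on it. On planned loss of 25–30%, this is the check likely to be run.

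The possible movement is 0.075–0.15 SD for an assumed CCT-only offset of 0.3–0.5 SD, and about zero if loss and offset are equal in both arms. These figures rest on assumed offsets and on loss at the planning rate.

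This is a cheap improvement of low-to-moderate priority. It matters because the 12-month d is meant to inform later power calculations. It does not affect the feasibility outcomes or the progression decision.

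**What to change.** Keep the chained-equations imputation and state that its model will include auxiliaries such as earlier BPRS-18 scores and session attendance. Add a delta-adjusted (tipping-point) version for 12-month BACS and UPSA-N:

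- Worsen the imputed values by a stated range, for example 0 to 0.5 SD, varied separately by arm so that CCT-only, control-only and both-arm departures are all shown.
- Report how the estimate and its CI move, and present this alongside the d offered for future power calculations.
- If the team wants the offset at which the estimate itself reaches zero, extend the range; for d = 0.50 that point lies at 1.67–2.0 SD (working, step 3).

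Whether to keep the 15% trigger is a matter of preference. So is the handling of therapy group in the imputation: with groups of six to eight there would be about 23–30 of them (180/8 to 180/6), nested in arm, so they are not a simple covariate.

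The cost is a sentence or two in the Missing data section or in the analysis plan before database lock, and modest extra programming. No new data are needed. The downside is that the reported d will look less certain.
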